#### Statistical analysis

2.15.2

1.Analysis procedures sample distribution: The number of dropouts and the rate will be described and analyzed for each data set, and the reasons for any dropouts are elucidated.2.Balance comparison: The subjects’ general data will be compared to assess the comparability of the two groups.3.Efficacy analysis: The subjects’ time to first flatus will be used as the primary outcome measure to assess the efficacy and safety of acupuncture in treating PGD. The means (χ) and standard (SD) deviations will be calculated to express the outcome measure, and the experimental and control groups will be statistically compared by two independent-sample *t* tests. Eight secondary outcomes will be applied to assess the efficacy of the acupuncture. Seven of these—namely, time to first defecation, abdominal pain, dosages of analgesia pump, abdominal distention, nausea, vomiting, and gastrointestinal hormones will be described usinḡχ± SD deviation and statistically compared between groups by Repeated Measures Analysis of Variance (RMANOVA). The statistical analysis of time to first defecation will be identical to that of time to first flatus. However, before performing RMANOVA, a sphericity test will be performed to determine whether the data are suitable for analysis by RMANOVA. If the data do not conform to the conditions of sphericity condition, the degree of freedom will be corrected using factor ε before the RMANOVA is performed. The categorical measure of psychological status will be analyzed using either the rank-sum test or Spearman's rank correlation.4.Safety analysis: In accordance with the definition of adverse events, specific adverse events, their severity level, causes, and explanations will be listed. The number of adverse events, and the incidence of adverse event will be statistically described. If inter group comparison is required, the χ^2^ test or Fisher's exact test will be performed.5.Methods of statistical analysis: An independent statistician analyzed the outcome data in accordance with the principle of intention-to-treat (ITT), that is, all subjects recruited in the group will be covered. The analysis of efficacy and safety indicators will be conducted following the principle of per-protocol (PP), that is, all subjects who completed the whole trial process without major protocol violations will be included. All statistical analysis complied with ITT population, and the results of ITT analysis will be compared with PP analysis to assess the sensitivity. All missing data will be analyzed using the last observation carried forward (LOCF) interpolation method. The qualitative data will be tested for normality, according to which independent *t* test or Mann–Whitney *U* test will be performed for groups comparison. Qualitative variables will be presented by the statistical description of χ ± SD of the normal distribution data, whereas qualitative variables will be recorded as the number of cases in each category. If the quantitative variables constitute repeated measures data, RMANOVA will be adopted for comparison, and the sphericity test will be performed to ascertain the applicability of, as well as to correct the data. The categorical variables will be represented by numbers (percentages) by χ^2^ test or Fisher's exact test *P* < .05 will be considered statistically significant on both sides in all the statistical tests. SPSS 25.0 software (SPSS, SPSS Inc, Chicago, IL) will be adopted for data statistical analysis.

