**Figure 2 F2:**
[figure not shown]
SPIRIT schedule of schedule of enrollment, interventions, and assessments. t1 is the day before surgery, t0 is the day of the surgery, t1 is 0 to 2 h after surgery, t2 is 2 to 6 h after surgery, t3 is 6 to 12 h after surgery, t4 is 12 to 24 h after surgery, t5 is 24 to 48 h after surgery, t6 is the day of the discharged, t7 is 2 weeks after patients discharged from the hospital.

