#### Secondary outcome

2.11.3

1.Time to first defecation: Researchers will inform the subjects and their families to assist in recording the interval between the time of subjects returning to the ward after the operation to the time of first defecation after operation.2.Abdominal pain: The Visual Analog Scale (VAS, Fig. 4) will be adopted to assess the degree of postoperative abdominal pain of subjects,^[27]^ which is to be recorded by researchers at t_1_ to t_5_.3.Dosage of analgesia pump: Considering that the use of analgesia pump will affect the degree of abdominal pain,^[33]^ therefore, the dosage of analgesia pump used by participants after operation will be recorded by researchers at t_1_ to t_5_.4.Abdominal distention: Likert scale (see Table 2) will be adopted to assess the degree of abdominal distention^[30,34]^ and recorded by researchers at t_1_ to t_5_.5.Nausea: The VAS scale will be employed to assess the degree of nausea^[27]^ and recorded by researchers at t_1_ to t_5_.6.Vomiting: The subjects and their families will help record the times of vomiting at t_1_ to t_5_.7.Gastrointestinal hormones: Blood samples will be taken 8 h before operation, 30 min after operation, and 24 h after operation to detect the level of gastrointestinal hormones. Enzyme-linked immunosorbent assay will be used to detect the levels of serum gastrin, motilin, ghrelin, 5-HT in the two groups. Three milliliters of blood will be harvested from the vein in the fasting state. The blood samples will be kept at ambient temperature for 30 min and then centrifuged at 3500 rpm for 10 min; the serum will be stored in a refrigerator at −70°C for testing. Serum samples will be collected by clinical centers, and relevant tests will be performed by Chengdu Lilai Biotechnology Co., Ltd.8.Psychological status: The Hospital Anxiety and Depression Scale (HADS) will be adopted to assess the psychological status of the subjects at t_0_ and t_6_.^[35]^ HADS has two subscales of anxiety and depression. There will be seven problems for anxiety and depression respectively. The anxiety and depression are expressed by the score of 0 to 7 points (no symptoms), 8 to 10 points (suspicious symptoms), 11 to 21 points (obvious symptoms). The first evaluation will be conducted 8 h before the operation, and the second one will be conducted on the day of discharge.

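### Vomiting, an episode count per window, is summarised only as mean ± SD and compared only by RMANOVA, so the plan never reports how many patients vomited (minor)

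*Protocol article*

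**What the plan says.** Section 2.11.3, item 6, defines the variable: "The subjects and their families will help record the times of vomiting" at t1 to t5. The legend of Figure 2 gives the windows: "t1 is 0 to 2 h after surgery, t2 is 2 to 6 h after surgery, t3 is 6 to 12 h after surgery", followed by 12 to 24 h and 24 to 48 h. Each patient therefore contributes five counts.

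Section 2.15.2, item 3, puts vomiting in the list "time to first defecation, abdominal pain, dosages of analgesia pump, abdominal distention, nausea, vomiting, and gastrointestinal hormones will be described" as mean ± SD and "statistically compared between groups by Repeated Measures Analysis of Variance (RMANOVA". The only contingency attached is a sphericity test; if it fails, "the degree of freedom will be corrected using factor ε before the RMANOVA is performed". Time to first defecation, in the same list, is sent back to the t test used for the primary outcome. No such exception is made for vomiting.

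Item 5 has a normality test leading to a t test or a Mann–Whitney test, but the sentence is worded for qualitative data. It then adds: "If the quantitative variables constitute repeated measures data, RMANOVA will be adopted for comparison". The same item provides χ² and Fisher tests for categorical variables. No yes/no vomiting variable is defined to which they would apply.

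**The concern.** RMANOVA with mean ± SD suits roughly symmetric continuous measurements. A count of vomiting episodes in a short window is likely to be zero for many patients, with a long right tail from a few who vomit repeatedly. Sphericity concerns the variances of differences between time points. Correcting the degrees of freedom for its failure does not deal with zeros or skew.

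Two things are at stake. The first is reporting: section 1 names vomiting among the symptoms of PGD and the comparator is granisetron, so readers will ask how many patients in each arm vomited. A mean ± SD per window does not answer that. The second is power: the group effect in RMANOVA rests on the mean number of episodes, which a few patients can dominate, so a drop in the number of patients who vomit may be missed.

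This is not a matter left to a later analysis plan, because the protocol itself assigns the method to this named outcome.

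**Working it through.** **Inputs.** From the protocol: five windows, 90 per arm, two-sided 0.05. The protocol gives no vomiting rate, distribution or expected effect, so there is no stated figure to reproduce. Assumed: a share p of patients vomits; the number of episodes in a vomiter is geometric (1, 2, 3, …) with mean m; episodes fall into the five windows in proportions 30/30/20/12/8%.

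**Step 1: is the summary readable?** For the 48 h total, mean = p·m. With m = 2.5, the geometric variance is (1 − 0.4)/0.4² = 3.75, so the second moment in a vomiter is 3.75 + 2.5² = 10, and SD = √(10p − (2.5p)²).

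| p | mean | SD |
|---|---|---|
| 10% | 0.25 | √(1.00 − 0.0625) = 0.97 |
| 25% | 0.625 | √(2.50 − 0.391) = 1.45 |
| 40% | 1.00 | √(4.00 − 1.00) = 1.73 |

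The SD exceeds the mean throughout, so mean − SD is negative for a variable that cannot be.

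**Step 2: share of zero cells.** A vomiter has no episode in a window of share w with probability 0.4(1 − w)/(1 − 0.6(1 − w)). This is 0.483, 0.483, 0.615, 0.746 and 0.821 for the five windows. The average chance of at least one episode is (0.517 + 0.517 + 0.385 + 0.254 + 0.179)/5 = 0.370. Zero cells are therefore 1 − 0.370p: 96% at p = 10%, 91% at 25%, 85% at 40%.

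**Step 3: power.** With complete data the RMANOVA group effect equals a t test on the patient total. Simulated power with 90 per arm:

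| Share vomiting | Episodes per vomiter | RMANOVA group effect | χ², any vomiting | Rank test on total |
|---|---|---|---|---|
| 25% vs 10% | 2.5 in both | 56% | 76% | 76% |
| 25% vs 10% | 1.5 in both | 64% | 77% | 77% |
| 40% vs 20% | 2.5 in both | 62% | 83% | 83% |
| 25% vs 10% | 1 in both | 77% | 77% | – |
| 25% vs 10% | 2.5 vs 1.5 | 91% | 77% | 82% |
| 25% vs 15% | 2.5 vs 1.5 | 72% | 39% | 47% |
| 40% vs 25% | 2.5 vs 1.5 | 92% | 59% | 75% |

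In the first three rows the loss against χ² is 20, 13 and 21 points. It is nil when each vomiter has one episode. In the last three rows the order reverses, and RMANOVA leads χ² by 14, 33 and 33 points.

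**Step 4: other count models.** With Poisson or negative binomial extra episodes and 78 or 90 per arm, the incidence-only loss against χ² is about 4 to 36 points over all scenarios and 7 to 29 in the middle ones. Against Fisher's test it runs from about −3 to 31. A negative binomial comparison of totals does not recover the loss: at 30% vs 12% it has 56 to 74% power, against 63 to 78% for RMANOVA.

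**Step 5: type I error.** With no difference between arms, the RMANOVA group effect rejects in 3 to 5% of simulated trials.

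**The case against.** The best defence has four parts.

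- **The test is valid.** This stands. Type I error is held, so a reader who infers that RMANOVA would produce false positives here goes too far.
- **The power loss is not general.** This also stands. A reader might infer that RMANOVA loses 10 to 25 points whenever acupuncture changes how many patients vomit. It does so only if episodes per vomiter stay essentially the same. A treatment that lowers both how many vomit and how often is at least as plausible, and then the mean-based test is the stronger one. Replacing it with any vomiting alone would be a trade-off, not a correction.
- **The excess of zeros is assumed.** True: the documents contain no vomiting rate. It holds across the assumed 10 to 40% range, but it cannot be called a stated fact about this trial.
- **Item 5 offers a non-normal route.** Partly true. Item 5 links mean ± SD to normally distributed data and names the Mann–Whitney test, so saying flatly that the plan has no alternative would overlook that text. But its wording concerns qualitative data, and the sentence on repeated measures then leads to RMANOVA. If the rank route was meant to cover vomiting, items 3 and 5 disagree.

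One might also extend the point to abdominal distention, a Likert grade handled the same way. RMANOVA and a rank test showed similar power there, so no loss is shown and a change is optional.

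**Conclusion.** The point holds as a minor one. The protocol fixes a per-window vomiting count to mean ± SD and RMANOVA, its safeguard does not address skew or zeros, and no planned output states how many patients vomited. That last gap does not depend on any assumed rate. The poor readability of mean ± SD does: it rests on about 10 to 40% of patients vomiting, with 2.5 episodes per vomiter in the figures above.

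The effect on power can go either way: a loss of roughly 10 to 25 points for an effect on incidence alone, little or none when vomiters have about one episode, and a gain when episodes per vomiter also fall appreciably. The documents do not say which pattern is expected, so no single figure for lost power can be charged to the plan. The outcome is one of eight secondary outcomes, and the sample size section claims no power for it.

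**What to change.** Before unblinding, amend section 2.15.2 as follows.

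1. Prespecify the proportion of patients with any vomiting over t1 to t5, that is 0 to 48 h after surgery. Compare the arms by the χ² or Fisher test already in the plan, with a risk difference and 95% CI. Start at surgery, not at treatment: treatment is given 30 min after surgery, inside t1, and a window count cannot separate episodes before it from those after.
2. Describe vomiting by n (%) and median (range).
3. Keep a comparison of the number of episodes alongside, since any vomiting is insensitive to an effect on repeat episodes.
4. Reword item 5 so that its normality and Mann–Whitney route refers to the intended type of data and agrees with item 3 on repeated measures.

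The cost is a wording change with no new data. The small downside is two vomiting comparisons on one secondary outcome.

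### The HADS analysis is left open between a rank-sum test and a correlation with no named variables, and it treats a 0-21 score with a pre-operative value as categorical; one baseline-adjusted comparison would serve better.

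*Protocol article*

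**What the plan says.** Section 2.11.3 (Secondary outcome), item 8, describes the HADS as two subscales, anxiety and depression, of seven questions each. The ranges for reading each subscale are "0 to 7 points (no symptoms), 8 to 10 points (suspicious symptoms), 11 to 21 points (obvious symptoms", so each is a score that runs up to 21. On timing it says: "The first evaluation will be conducted 8 h before the operation, and the second one will be conducted on the day of discharge".

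Section 2.15.2 (Statistical analysis), item 3, gives the outcome its purpose: "Eight secondary outcomes will be applied to assess the efficacy of the acupuncture". Psychological status is one of the eight. The other seven have their own methods, and this one is assigned as follows: "The categorical measure of psychological status will be analyzed using either the rank-sum test or" Spearman's rank correlation.

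Item 5 of the same section adds two general rules. For categorical variables: "The categorical variables will be represented by numbers (percentages) by" the chi-square or Fisher's exact test. For repeated measurements: "If the quantitative variables constitute repeated measures data, RMANOVA will be adopted for comparison".

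**The concern.** The outcome is meant to show whether acupuncture and granisetron differ in anxiety and depression at discharge. The stated analysis fits that aim poorly in three ways.

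- **Open choice.** Two methods are offered with no rule for choosing, and one is a correlation whose variables are not stated. Item 5 adds to the doubt, because its chi-square or Fisher rule could also be read as covering an outcome called categorical.
- **Loss of score information.** If a categorical measure means the three bands, a rise from 0 to 7 counts as no change, while a rise from 7 to 8 counts as a change of category.
- **No stated role for the baseline score.** The same scale is completed before surgery, but neither named method has a place for that value.

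At stake is precision and a readable effect estimate for this one outcome. A real difference could be missed that the collected data could show, and a p-value or a correlation coefficient would not tell a clinician how many points separate the groups.

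**Working it through.** The protocol states no power, SD or expected difference for the HADS, so there is no figure of its own to reproduce. Two checks follow.

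**Check 1: what Spearman can mean here.** Let g be the group indicator, R the midranks of the HADS outcome, n1 and n0 the group sizes, and N = n1 + n0. Write S for the sum of (g − mean g)(R − mean R), and Q for the sum of (R − mean R)².

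- Spearman: rho = S / √[(n1·n0/N)·Q].
- Tie-corrected rank-sum: z = S / √[(n1·n0/(N(N − 1)))·Q].
- Dividing one by the other: z = rho·√(N − 1).

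With 90 per group (sections 2.1 and 2.7), N = 180 and √179 = 13.38. In one simulated data set on the three bands, rho·√179 = −2.456, so rho = −2.456/13.38 = −0.184. Referred to the normal distribution, this gives p = 0.01406. The rank-sum test without continuity correction gives the same p = 0.01406.

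Spearman between group and band is therefore the rank-sum test under another name. Spearman between, say, pre-operative and discharge HADS, or HADS and time to first flatus, answers a different question. The text does not say which is meant.

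**Check 2: efficiency.** From the document: 90 per group, two-sided 5% level, bands 0-7, 8-10 and 11-21. Assumed: SD 3.5, true difference 1.5 points, control mean 5, 7 or 9 (same mean before surgery), and correlation between the two measurements 0.3, 0.5 or 0.7. Scores were drawn from normal distributions, rounded and limited to 0-21, with 2000 runs per setting. The Monte Carlo standard error is √(0.5·0.5/2000) = 1.1 points at 50% power and √(0.05·0.95/2000) = 0.5 points at the 5% level.

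Power (%):

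| Control mean | Correlation | Rank-sum, three bands | Rank-sum, raw score | ANCOVA with baseline |
|---|---|---|---|---|
| 5 | 0.3 | 50.1 | 77.5 | 82.0 |
| 5 | 0.5 | 51.4 | 79.0 | 89.4 |
| 5 | 0.7 | 49.3 | 79.4 | 97.0 |
| 7 | 0.3 | 65.4 | 79.8 | 85.0 |
| 7 | 0.5 | 64.3 | 78.8 | 89.3 |
| 7 | 0.7 | 65.1 | 78.7 | 97.4 |
| 9 | 0.3 | 71.8 | 80.4 | 85.3 |
| 9 | 0.5 | 71.4 | 79.3 | 90.9 |
| 9 | 0.7 | 71.2 | 78.7 | 97.8 |

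With no true difference, the banded rank-sum test rejected in 4.6% to 5.8% of runs and ANCOVA in 4.4% to 6.1%.

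Hand check of the ANCOVA column: the unadjusted standard error is 3.5·√(2/90) = 0.522, and 1.5/0.522 = 2.875. Dividing by √(1 − r²) gives 3.01, 3.32 and 4.03 for r = 0.3, 0.5 and 0.7. Subtracting 1.96 gives normal-theory power of about 85%, 91% and 98%. Simulated values are slightly lower at control mean 5, where the floor at zero bites.

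Differences in power:
- Banding alone (raw rank-sum minus banded): from 78.7 − 71.2 = 7.5 to 79.4 − 49.3 = 30.1 points.
- ANCOVA over the raw-score rank-sum: from 82.0 − 77.5 = 4.5 to 97.8 − 78.7 = 19.1 points.
- ANCOVA over the banded rank-sum: from 85.3 − 71.8 = 13.5 to 97.0 − 49.3 = 47.7 points.

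**The case against.** The strongest reply is that the plan already contains a sound test. A reader might infer from the wording that the psychological outcome can get no valid answer. The document does not support that: the rank-sum test is named first, it is a legitimate comparison of randomised groups on an ordered outcome, and its type I error is close to 5%. Leaving baseline out costs precision but does not bias a randomised comparison.

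Four other strong readings also fail.

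- *Spearman cannot compare groups.* It can if one variable is the group. The defect is that the variables are not stated.
- *The test will be picked once results are known.* The text gives no time for the choice. Section 2.8 keeps statisticians unaware of allocation, and section 2.13 keeps them from the data during assessment.
- *The baseline is discarded.* The article only states no use of it. It condenses a fuller protocol, and an analysis plan not shown could add adjustment, so the silence is not itself an error.
- *Banding is certain.* Calling the measure categorical points that way, but nowhere is the rank-sum test said to be run on the bands. On the raw score, much of the loss disappears.

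It can also be said that ANCOVA for a bounded scale is partly a preference and that the power figures rest on assumptions. Both are fair. What stands is an unresolved either/or, one branch of which is redundant or off the question, and a named method that makes weaker use of data the trial collects anyway.

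**Conclusion.** The concern holds in a limited form. The HADS analysis should be settled as one group comparison; Spearman adds nothing as written, and neither named method reports a difference in score points. The rank-sum option is valid but inefficient. Against baseline-adjusted ANCOVA, the banded version gives up about 13 to 48 percentage points of power, and the raw-score version about 4 to 19.

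These sizes depend on the assumed SD of 3.5, difference of 1.5 points, control mean of 5 to 9 and correlation of 0.3 to 0.7. To say that most of the information is lost would hold only toward the lower means or higher correlations. Of the components, the open choice and the unspecified correlation are certain from the text, banding is likely, and the absence of baseline adjustment is only unstated. The consequence is confined to one of eight secondary outcomes; the primary comparison, the sample size and the safety analysis do not depend on it.

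**What to change.** In section 2.15.2, item 3, replace the HADS sentence with a single analysis. For each subscale separately, compare the 0-21 discharge score between groups by ANCOVA with the pre-operative score as covariate, and report the adjusted mean difference with its 95% confidence interval. Give the three bands as counts and percentages by group, for description only. Delete Spearman, and state that the general rule for categorical variables in item 5 does not govern the HADS comparison.

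If a rank-based analysis is preferred as a check, say that it is run on the raw score. The cost is one or two sentences; both measurements are already scheduled, so no new data, visits or patients are needed.

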### Elimination standard

2.6

Subjects will be eliminated from the trial if meeting any of the following conditions:

1.laparoscopy must be converted to laparotomy;2.refusal to continuous treatment for various reasons;3.with severe syndromes (e.g., biliary fistula and peritonitis) during the treatment;4.transferred to other specialist treatments;5.having become comatose or die;6.cannot participate in the follow-up for various reasons;7.researchers accidentally included the subjects not meeting the inclusion criteria;8.less compliance with the treatment regulations and failed to provide information that might be critical to the evaluation.

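### Section 2.15.2 item 5 contradicts itself on the analysis population, and its per-protocol sentence, the only one that assigns safety by name, would leave eliminated patients out of the adverse event analysis if followed

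*Protocol article*

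**What the plan says.** Protocol article, section 2.15.2 (Statistical analysis), item 5 makes three statements about populations, one after another:

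- (a) ITT for outcome data, with everyone recruited counted in: "An independent statistician analyzed the outcome data in accordance with the principle of intention-to-treat (ITT), that is, all subjects recruited in the group will be" [...].
- (b) "The analysis of efficacy and safety indicators will be conducted following the principle of per-protocol (PP"; the PP set is then defined: "all subjects who completed the whole trial process without major protocol violations will be included".
- (c) "All statistical analysis complied with ITT population, and the results of ITT analysis will be compared with PP analysis to assess the sensitivity".

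Item 3 (efficacy) and item 4 (safety) of the same section name no population. Item 4 provides for a listing of specific adverse events with severity and causes, a description of their number and incidence, and a chi-square or Fisher test if a comparison between groups is needed.

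Section 2.6 (Elimination standard) lists patients who are taken out of the trial. The list includes those "with severe syndromes (e.g., biliary fistula and peritonitis) during the treatment", those "having become comatose or die", those transferred to other specialist care, and those showing "refusal to continuous treatment for various reasons". Section 2.12 requires all adverse events to be entered on the case report form, and complications to be recorded up to two weeks after discharge.

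**The concern.** A reader who needs to know which patients enter the main analysis gets two answers from item 5. For efficacy this is a drafting conflict that should not survive into the analysis. For safety it matters more. Statement (b) is the only sentence that links the safety indicators to a named set, and that set consists of completers. A patient who develops peritonitis, becomes comatose, dies, or refuses to go on with treatment is eliminated under section 2.6 and so has not completed the trial. These are among the patients whose events a safety analysis exists to count. The article gives the assessment of acupuncture's safety as one of the trial's aims, so the denominator for that assessment should not be in doubt.

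**Working it through.** **Step 1: the three statements side by side (section 2.15.2 item 5).**

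| Statement | Scope | Population |
|---|---|---|
| (a) | outcome data | ITT, all recruited |
| (b) | efficacy and safety indicators | PP, completers without major violations |
| (c) | all analyses | ITT, with PP compared as sensitivity |

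Statements (a) and (c) agree. Statement (b) conflicts with (c) for efficacy and for safety. Only (b) mentions safety explicitly; (c) covers it by implication. Items 3 and 4 do not settle the matter, since neither names a set.

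**Step 2: who would leave the safety analysis under (b).** The PP definition requires completion of the whole trial process. Section 2.6 takes out patients with severe complications, coma or death, transfer, or refusal of treatment. The article does not say outright that an eliminated patient is outside the PP set, but a patient taken out of the trial cannot be said to have completed it.

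**Step 3: scale.** The plan has no figure for the PP set. Inputs are 180 patients, 90 per group, and 15% dropout (section 2.15.1). Assumption: the PP loss equals the planned dropout and is equal in both arms.

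- Outside PP: 180 × 0.15 = 27. Inside PP: 180 × 0.85 = 153.
- Per arm inside PP: 90 × 0.85 = 76.5.

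**Step 4: what decides the bias.** In one arm of n treated patients let a have an event, let f be the share of those a patients who fall outside PP, and let d be the share of all patients who fall outside PP.

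- Incidence in all treated patients: a / n.
- Incidence in PP: a(1 − f) / [n(1 − d)].
- Ratio of PP to all treated: (1 − f) / (1 − d).

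With d = 0.15, and with 4 patients with events among 90 as a pure assumption (4/90 = 4.4%):

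| f (assumed) | ratio | PP incidence |
|---|---|---|
| 0 | 1/0.85 = 1.18 | 4/76.5 = 5.2% |
| 0.15 | 0.85/0.85 = 1.00 | 3.4/76.5 = 4.4% |
| 0.50 | 0.50/0.85 = 0.59 | 2/76.5 = 2.6% |
| 0.75 | 0.25/0.85 = 0.29 | 1/76.5 = 1.3% |
| 1.00 | 0 | 0% |

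Harm in an arm is understated when f exceeds d and overstated when f is below d. The article gives neither an adverse event rate nor f, so no row can be chosen for adverse events overall. For coma and death f is 1 by the elimination list itself, so under (b) those events would count as zero in both arms. How a comparison between arms would shift depends on f and d in each arm, which are unknown.

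**The case against.** The best defence is that (c) comes last, covers everything, and gives PP the sensitivity role, while (a) also says ITT. On that reading (b) is a clumsy way of saying that a PP analysis will be run as well. Item 5 has other wording slips, such as a normality test for qualitative data, so loose drafting is plausible. This stands: ITT main with PP as sensitivity is the most coherent reading.

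Four stronger inferences are tempting, and the article does not support them:

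- *That the plan does remove serious events from the safety analysis.* This follows only if (b) governs, and the text does not say that it does.
- *That serious events would go unseen.* Section 2.12 has them recorded, and item 4 calls for an event listing with no PP restriction. At risk are the analysed numerator and denominator, and a between-group test that is itself conditional.
- *That the sponsor is free to headline whichever population looks better.* Statement (c) names ITT for all analyses and commits to comparing the two sets.
- *That harm is understated in whichever arm loses more patients.* Step 4 shows that the bias turns on how far the losses are related to events, not on their number.

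It is also fair to say that treatment is given once. After a single injection, a control patient has no later trial dose to refuse, so stopping treatment because of an adverse event is mainly possible in the acupuncture arm while needles are in place. This narrows one route out of the PP set. Elimination for severe complications, coma, death or transfer remains open in both arms.

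Finally, a full definition of a safety set can be left by an article to the full protocol or SAP, and its absence alone would be no finding. The finding here is that the article does assign safety to a set, and to an unsuitable one.

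**Conclusion.** The contradiction is certain on the text: (b) cannot be reconciled with "All statistical analysis complied with ITT population". As written, (b) is also wrong for safety, because a completers-only set excludes patients eliminated for the most severe outcomes. That this exclusion would actually happen is not established, since (c) supports ITT as the main analysis. If (b) were followed, about 27 of 180 patients would be outside the safety analysis, assuming that PP losses match the planned 15% dropout. Neither the size nor the direction of the resulting bias in overall adverse event incidence, or in the comparison between arms, can be computed from the article.

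**What to change.** In section 2.15.2 item 5:

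1. Delete the sentence that assigns efficacy and safety indicators to PP, and keep the definition of the PP set for use in point 3.
2. State that primary efficacy is analysed on all randomised patients in the group to which they were allocated (ITT).
3. State that PP is a sensitivity analysis of efficacy only.
4. State that safety is analysed on all patients who received acupuncture or granisetron, by treatment received, and that every treated patient who meets any item of the section 2.6 list stays in this set. That includes patients found to be wrongly included and those with poor compliance.

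A cross-reference to this set in item 4 would remove any remaining doubt. The cost is a few sentences. No extra data are needed, because section 2.12 already has the events recorded.
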